# A2. PURPOSE OF PROTOCOL

**Goals of the Proposal**

There are two aims associated with this proposal. The first aim is to characterize the relationships between clinical phenotype through a series of questionnaires, genetic background, representation of phenotype in induced pluripotent stem cells and correlation to drug response in ALS patients. The second aim of this proposal is to identify new end points for ALS clinical trials by comparing the self reported ALS Functional Rating Scale (ALS FRS) to patient voice recordings and data collected from wearable technologies (accelerometers).

In the first phase of the study these goals will be accomplished by obtaining a patient’s consent to collect tissue samples (blood) for DNA sequencing and molecular profiling (RNA and protein) and a skin biopsy to develop an induced pluripotent stem cell line (iPS) for banking and high content drug screening at ALS TDI.

In this phase of the study participants will also be asked to report ALS FRS and provide a voice recording on a monthly basis and to wear accelerometers on their wrists and ankles for one week per month to collect unbiased movement data. These data will be compared to the ALS FRS questionnaire, a self-reporting web based questionnaire to monitor disease progression.

A database will be developed to link a patient’s genetic data, molecular data, and high content screening data with disease progression assessment methodologies.

In the second phase of the study (Extension Program) an additional cohort of early stage ambulatory participants will be recruited to increase the power to detect changes in disease progression using the data from a series of questionnaires, self reported ALS FRS, voice recordings, and wearable technologies (accelerometers).

300 participants will be recruited in the first phase of the study and 700 participants will be recruited in the second phase of the study in order to obtain statistically meaningful data for a total of 1000 participants.

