**Consent Phase II study participants**

There is no site visit or clinical visit associated with phase II participants.

If a participant responds to the recruitment announcement they will have provided their name, email address, and phone number.

The system will send a text message to the participant’s phone with a pin number and URL to log into a secure webportal with their preliminary information. The webportal will house all of their data for the study. The text message will serve as an authentication of the identity of the participant.

The webportal will be broken into sections. At the bottom of each section there will be a statement asking if the participant understand all in information provided in that section with a check box to check in order to move on. If a participant has questions an email link and phone number will be provided to contact a study coordinator to clarify information.

The following sections will be broken down:

- - Section I: Overview of the study, its rationale and objectives, and that participants will be asked to participate in the study for 18 months or until they are no longer able. They can stop at anytime.
  - Section II: Describe the rationale and purpose behind, the genome sequencing.
  - Section III: Describe the rationale and purpose for the development of induced pluripotent stem cell lines.
  - Section IV: Describe the rationale and purpose behind collecting monthly self reported ALS FRS.
  - Section VI: Describe the rationale and purpose on collecting monthly voice recordings.
  - Section VII: Describe the rationale and purpose behind collecting monthly accelerometer data.
  - Section VIII: Describe the rationale and purpose behind asking participants to fill out the demographic and medical questionnaires.
  - Section IX: There are minimal risks associated with participation in the study.
  - Minor discomfort may be experienced during the in-home venous blood collection.
  - Section X: There are no treatments being administered as part of the study.
  - Section XI: Participation in the study is voluntary. A decision to not participate will not result in any penalty or loss of benefits.
- Once all the sections have been read and the boxes checked that the participant understands all the information for the study they will be asked to sign the online consent form
- When the forms arrive back into our system the consent form is then signed electronically by the PI, [name].

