**Rationale around enrolling 700 participants in the second phase and collecting 10,000 data points:**

The most common primary end point in ALS clinical trials is ALS FRS. According to post hoc analysis on dozens of ALS clinical trials it takes 450 patients enrolled in a 12 month study to detect a 30% change in the slope of monthly reported ALS FRS. In order to detect meaningful changes in ALS disease progression slope as small as 20%, a cohort as large as 700 people with ALS would be required. The ALS FRS is a 12 point questionnaire with each question scored from 0-4, 4 being a perfect score. This is then summarized into a single score with a maximal value of 48 points per month for a perfect score. This represents 100,000 data points summarized to 8,400 individual scores over 12 months for 700 patients. In order to compare monthly reported ALS FRS with a potentially new outcome measure such as data from accelerometers the study will require a similar design to compare ALS FRS to accelerometers. The goal of the extension study is to enroll a second cohort of participants, a validation cohort, to collect 15,500 data points for ALS FRS and accelerometers in order to determine the sensitivity of these two potential outcome measures in a statistically meaningful way.

[figure not shown]

Data Analysis: ALS TDI has a robust data management system that assigns a unique identified and barcode to each tissue sample that is generated from any source. Each unique identifier can then have multiple clinical attributes associated with it including age, gender, age of diagnosis, site of onset, medication history, tissue type etc. ALS TDI has robust genomics capabilities including Affymetrix RNA profiling and whole genome sequencing data infrastructures built in SciTegic Pipeline pilot and a backend using Bioconductor and R code. Data from the project will be entered into these systems for downstream data quality control and processing. The Bioconductor packages have a suite of clustering tools to analyze multidimensional complex data structure to identify patterns in genomics, RNA profiling and clinical data obtained from this project.

The scientific rationale around control group will not be a 1:1 basis but would be of scientifically meaningful controls for example a twin of a participant with spontaneous ALS.

Data Follow Up:

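### The 20% slope sensitivity claimed for 700 participants does not follow from the protocol's own benchmark of 450 for 30%; under the same assumptions 700 corresponds to about 24%

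*Protocol*

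**What the plan says.** The protocol, A4 (Statistical Considerations), has a paragraph on the rationale for 700 participants in the second phase. It opens with a benchmark attributed to post hoc analysis of ALS trials: "it takes 450 patients enrolled in a 12 month study to detect a 30% change in the slope of monthly reported ALS FRS". The next sentence sets the extension target: to detect "changes in ALS disease progression slope as small as 20%, a cohort as large as 700 people with ALS would be required". The paragraph then counts the data these participants would yield: "This represents 100,000 data points summarized to 8,400 individual scores over 12 months for 700 patients".

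Both figures concern the slope of the ALS FRS, and both are tied to 12 months. The paragraph gives no alpha, power, slope SD, dropout allowance or formula for either figure. On a comparison group, A4 says only that "The scientific rationale around control group will not be a 1:1 basis", with no ratio. A2 (Goals of the Proposal) gives the overall plan: "300 participants will be recruited in the first phase of the study and 700 participants will be recruited in the second phase".

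**The concern.** The target effect falls by a third, from 30% to 20%, but the cohort rises only from 450 to 700, a factor of 1.56. At fixed error rates and variance, a fall of that size calls for a factor of 2.25. The two sentences therefore do not agree unless something else changed between them, and the protocol does not say that anything did.

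The 20% figure is the only quantitative reason given for choosing 700, and A3.1 gives greater power to detect progression as a goal of the extension. What is at stake is the accuracy of that rationale: a reader would credit the cohort with a finer sensitivity than the cited benchmark supports.

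**Working it through.** **Inputs, all from A4**
- Benchmark: 450 patients, 12 months, 30% change in ALS FRS slope.
- Extension: 700 participants, 20% change, with scores counted over 12 months.
- Alpha, sidedness, power, slope SD relative to mean slope, design: not stated. They are taken as equal for both figures, so they cancel in the ratio.

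**1. Confirming the time frame.** 700 × 12 monthly scores = 8,400, as stated. 8,400 × 12 items = 100,800, which matches the rounded 100,000. So the paragraph does use 12 months for the 700, as for the 450.

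**2. Trying to reproduce 700.** With everything else fixed, N is proportional to 1/effect²:

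N = 450 × (30/20)² = 450 × 2.25 = 1,012.5, so about 1,013 (1,014 as two equal arms).

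The stated 700 is not reproduced. The shortfall is (1,013 − 700)/1,013 = 31%. Re-solving a two-group comparison with the SD back-calculated from 450 for 30% gave 1,014 at each setting tried: two-sided 5%, one-sided 5% and two-sided 10%, each with 80%, 85% and 90% power. Other simple rules do not give 700 either. Treating the change as a log ratio gives 450 × (ln 0.7/ln 0.8)² = 1,150. Simple proportion gives 450 × 30/20 = 675.

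**3. What 700 corresponds to.** 30% × √(450/700) = 24.1%.

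**4. Power of 700 for a 20% change.** The power behind the 450 is not given, so a range is shown, assuming two-sided 5%:

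Power = Φ[(1.960 + z_power) × (20/30) × √(700/450) − 1.960], where (20/30) × √(700/450) = 0.831.

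| Assumed power of 450 for 30% | Power of 700 for 20% |
|---|---|
| 80% | Φ(0.37) = 64% |
| 85% | Φ(0.53) = 70% |
| 90% | Φ(0.74) = 77% |

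**5. What would have to differ for 700 to be right**
- *Error rates:* 450 at two-sided 5% and 85% power, with 700 at one-sided 5% and 80% power, gives 697. Two-sided 90% paired with one-sided 85% gives 693.
- *Follow-up of 18 months:* the sum of squares of monthly times about their mean rises from 182 to 570. If f is the share of the 12-month slope variance due to residual noise, N = 1,012.5 × (1 − f + f × 182/570). This equals 700 at f = 0.45. The range is 1,013 at f = 0 to 323 at f = 1.
- *Population:* for a percentage change in slope, N scales with the squared ratio of slope SD to mean slope. That ratio would have to be √(700/1,012.5) = 0.83 times its value in the source trials, about 17% lower.

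**The case against.** The strongest reply is that A4 shows no calculation for the 700 and does not say it was scaled from the 450. The benchmark comes from past trials, while the extension recruits early-stage ambulatory participants and excludes those with symptoms beyond 36 months or on non-invasive ventilation. Their relative slope variance may well differ. Participants are also followed for longer than a year: in the phase II consent section, "participants will be asked to participate in the study for 18 months or until they are no longer able". And a figure that follows the A4 paragraph was not available for this review.

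Much of this stands. It makes 1,013 and 24% conditional on common settings. It does not remove the inconsistency, because none of these differences is stated as the basis of the 700. The relative variance could as easily be higher as lower. The paragraph counts 12 months, not 18.

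Three stronger readings are tempting and are not supported.
- A reader might infer a plain arithmetic slip, with 700 obtained by simple proportion. That rule gives 675, and with no working shown the cause is a guess.
- A reader might infer that a null result at 20% will be misread. The protocol plans no such test: no treatment is given, there is no randomised comparison, and the extension aims to compare the sensitivity of ALS FRS and accelerometers.
- A reader might let the two phases together carry the claim, since A2 speaks of recruiting "in order to obtain statistically meaningful data for a total of 1000 participants" and 30% × √(450/1,000) = 20.1%. But A4 ties the 20% to the 700 and defines the extension as a separate validation cohort, and A3.2 gives the phases different eligibility.

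**Conclusion.** The point holds as an internal inconsistency. With alpha, power, relative slope variance, design and 12-month follow-up equal for both figures, the benchmark implies about 1,013 for a 20% change. On the same basis the planned 700 corresponds to about 24%, with roughly 64% to 77% power for 20% if the benchmark carried 80% to 90% (two-sided 5%, assumed).

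These figures test one sentence of the protocol against the one before it. They carry over the unknown contrast of the source trials and are not a full sample size for an observational cohort. They are no ground for saying the study must enrol 1,013. The sentence should be corrected because it is the stated reason for the cohort size. It does not block the study, since no specified analysis or decision rests on the 20%.

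**What to change.** Keep enrolment at 700 and restate the A4 sentence along these lines: *Scaled from 450 for 30% under the same assumptions, 700 participants over 12 months correspond to a change of about 24%; a 20% change would need about 1,013. This benchmark comes from clinical trials and is carried over to an observational cohort.* Giving the alpha and power behind the 450 would let a reader check it.

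Alternatively, keep the 20% and state the assumptions under which 700 achieves it: alpha, power, slope variance in early-stage participants, and follow-up. The 20% should not be moved to the combined 1,000, because that would undo the separation of the validation cohort.

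The cost is one or two sentences in A4 and, under the first option, a less favourable stated sensitivity. No participants, procedures or analyses change.

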#### A5. POSSIBLE BENEFITS

There are several beneficial aspects of enrolling in the program. One important aspect is having ones whole genome sequenced as part of the program. The vast majority of ALS cases are sporadic in nature (~90%) with no known genetic association. For patients with the familial form of the disease more than 70% of these cases now have an ability to identify the underlying genetic cause that is associated with about 27 genes. Recent data suggests that it is very common for sporadic cases of ALS to have mutations associated with common ALS genes including SOD1 and C9ORF72. This will allow these patients to know if they have mutations in genes commonly associated with ALS. For sporadic cases with no known mutations the long term goal of clustering the data into clinical phenotypes based on iPS cell phenotypes may allow us to identify new genetic risk factors associated with the disease that maybe relevant to specific ALS cases and their family members.

Another benefit is that the program will bank pluripotent stem cell lines for each patient after reprogramming. From a clinical perspective this technology is still very new and future application to the treatments of patients is quickly evolving. A banked stem cell may prove valuable for a patient as new applications are developed and maybe useful for other family members in the future.

Finally the development of research tools for high content screening from a patient’s own cells could lead to early opportunities for drug repurposing for a patient in the program.

There is a significant benefit for the ALS community as a whole. The construction of a comprehensive database that couples clinical phenotype to genomic sequence data and phenotypic screens on patient cell lines will lead to a more understanding of disease mechanisms, drug development opportunities, and effective treatments for patients. The coupling of genomics to these endpoints will also lead to rare genetic associations with ALS that have not been characterized.

#### A6. POSSIBLE RISKS AND ANALYSIS OF RISK/BENEFIT RATIO

The actual clinical procedures have little risk for patients outside of bleeding from the skin biopsy which in some cases may require a suture to stop the bleeding, and the potential for some scarring around the skin biopsy. There may be localized discomfort from the blood draws.

The most important factor to consider is the need for genetic counseling should a patient choose to want to know any mutations that are identified in the genome sequencing component of the proposal. All ALS clinics have genetic counseling available and for those patients that have a desire to discuss their genetic information ALS TDI will facilitate genetic counseling at their ALS clinical prior to discussions.

With human subjects research, there is always the risk of the loss of confidentiality. ALS will take all reasonable precautions to protect the participant and their data.

#### A7. STUDY LOCATION

All interviews will be conducted over the phone by the project coordinator at ALS TDI.

Patient consent forms and waivers will be distributed to patients and collected via Fedex. The verification of written consent and verbal consent will be conducted at ASL TDI on the day of the visit prior to transport to MGH for tissue collection.

Blood and skin will be collected at MGH Hospital according to the study protocols.

No further patient follow up will be required unless a patient requests to discuss the results of the genetic information.
